## 6.4 Monitoring plan

In this project most of the procedures are built into the app and are made automatic. Questionnaires and reminders to answer the questionnaires will be pushed through the app and data will be retracted from the continuously saved analytics. Supplement 3 shows the Case Report Form with variables that will be extracted for each individual.

All data is pseudonymized and stored in a three-level categorized and double-encrypted server to ensure personal integrity and security. The research study is managed as a separate module of the system, which enables automatic and anonymous communication with the research subjects, and safe data transfer limited to the research purposes on an individual- and group level without sharing any personally identifiable information. Transfer of data from the server to the principal investigator will be made through a regulated and monitored web platform with obligatory electronic identification for access.

Time points for the specific questionnaires are shown in table 1. The time for pushing out questionnaires is programmed at start and controlled by the investigators.

Routines for documentation on adverse effects is described in the IB (supplement 3). All involved personnel: quality manager, health coaches, webinar hosts and else are introduced to the IB and trained in the documentation process.

The IB will be saved as an online file to make sure everyone has the latest version. Changes made to the IB are highlighted and logged at the last page. Before changes are made a version of the IB is saved, named with version number and date.

Parts of the monitoring reports will be published in scientific journals as a process evaluation describing implementation factors, reach and engagement.

## 7. Statistical design and analysis

### 7.1 Analysis population

For the endpoint well-being an intention-to-treat approach will be applied. By using mixed model for repeated measures all subjects with two or more measurements will be included in the analysis and manual imputation is not needed. For the intermediate outcomes dietary habits, physical activity, and mental health only subjects who have set up change goals within the area will be analysed.

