#### 4.5 Steps that will be taken to control or mitigate the risks.

The risks of data insecurity will be handled cautiously, and the subjects will be informed about the measures taken to secure confidentiality and trustworthiness with an informed consent. The system is built to never share any personal data with any party, applying pseudonymization with anonymous ID numbers for all users. Personal data will be stored in a double-encrypted, three-level categorization system to ensure data security, and personal integrity by separating personally identifiable information from personally sensitive information. The system has strictly limited access to personal data with regulated, monitored, and logged functions that enable access to limited and anonymous data for authorized parties only. For example, authorized researchers and health coaches must identify themselves with electronic identification to access strictly limited and anonymous data, only relevant to research or health coaching purposes. Overall, the system complies with the current requirements for security and monitoring, which is ensured by regular security checks and penetration testing by an external independent party.

The risk of perceived stress, excessive behaviors, anxiety, a feeling of failure, hopelessness, and low self-esteem are mitigated through support by setting realistic and progressive goals, encouragement, information, and webinars about behavior change and healthy habits. Alerts and report functions are built into the system to alarm excessive habits and low well-being score. World Health Organization's well-being index (WHO-5) (34) will be sent out monthly to the user. When low well-being is reported (score 50 or below) recommendations to healthcare providers is presented to the user.

A requirement for working as a health coach is owning a higher-level education as a health professional including at least 7.5 ECTS in health counselling. A mandatory introduction course for all new health coaches is produced by the Head of health coaching and Quality manager and covers elements of mandatory security measures based on the risk assessment. Prior to the coach session, the coach gets data on the user's action plan covering well-being scores and details about the user's action plan. A protocol and a guide for how and where to refer individuals in need of health care have been produced by the quality manager.

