## 6.3 Procedures for data collection

### 6.3.1 Procedures

This investigation will take place outside the clinical practice. Data will be collected by self-reported instruments (questionnaires) and analytics from the digital service. An exception from self-reported measures is that an activity monitor will be used to measure physical activity and sedentary behavior besides self-reported instruments. Supplement 6 Case Report Form shows the included questionnaires with details on specific questions and response alternatives. Reminders to answer the questionnaires will be pushed out weekly for 4 weeks until the subject has answered (max 4 reminders). The activity monitor will be posted to the subjects together with instructions and a log to write the time when the monitor was put on and off during the day. It should be placed on the thigh and worn for 7 consecutive days. The subject will be asked to fill out the diary for wake-up time and bedtime, and for major physical activities performed during the day.

Answering questionnaires and wearing the activity monitor is voluntarily, and if the subject does not answer it will not affect his/her use of the app.

There is a risk of selection bias affecting the results. We believe highly motivated subjects (responders) possibly answer the questionnaires to a larger extent than subjects facing more challenges.

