|                              | Living area                                                      | No specific                                     | x                  |   |   |   |    |    |    |
|                              | Country of origin                                                | No specific                                     | x                  |   |   |   |    |    |    |
| Well-being and mental health |                                                                  |                                                 |                    |   |   |   |    |    |    |
|                              | Well-being                                                       | WHO-5 Well-being index                          | x                  | x | x | x | x  | x  | x  |
|                              | Stress                                                           | The Karolinska Exhaustion Disorder Scale (KEDS) | x                  |   | x | x | x  | x  | x  |
|                              | Burnout                                                          | The Oldenburg Burnout Inventory (OLBI)          | x                  |   | x | x | x  | x  | x  |
|                              | Sleep                                                            | Self-reported number of hours at sleep          | x                  |   | x | x | x  | x  | x  |
|                              |                                                                  | Sleep diary*                                    |                    |   |   |   |    |    |    |
|                              |                                                                  | ISI – Insomnia Severity Index                   | x                  |   | x | x | x  | x  | x  |
|                              | Mental balance                                                   | No specific                                     | x                  |   | x | x | x  | x  | x  |
| Goal achievement             |                                                                  |                                                 |                    |   |   |   |    |    |    |
|                              | Confidence in reaching the goal                                  | No specific                                     | x                  |   | x | x | x  | x  | x  |

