### 7.3 Analytical procedures

Change in the endpoint well-being (as total score) and the intermediate outcomes dietary habits, physical activity, and mental health, will be analysed across time and between groups using mixed model for repeated measures, and reported as estimates with confidence intervals. The model will include intervention level and time (0, 6, 12, 18 and 24 months).

To investigate correlations and associations of demographic factors and user engagement with behavior change, mental balance, and well-being, structural equation modelling and mixed models will be applied.

Regression analysis and mixed models will be applied to evaluate mediating factors and responsiveness. These analyses will explore if high levels of motivation, self-efficacy and reduced perceived barriers mediates improvements in reaching the self-identified goal, behavior, mental health, and well-being and whether improvements in motivation, behavior, and mental health mediate well-being. Cut off values for the intermediate outcomes will be derived based on baseline values and findings from similar studies.

The threshold for statistical significance will be set at  $p < 0.05$ .

Qualitative data (chat groups and dialogues with included actors) will be analyzed by content analysis (46).

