### 7.4 Sample size calculation

The endpoint well-being will be assessed using the WHO-5 Well-being Index (34). In our pilot study the mean score at baseline was 55. The instrument has to our knowledge not been applied on a general Swedish population. In Danish general population surveys, the mean WHO-5 score was 60-70 ( $sd=19.0-19.9$ ) (36, 47, 48). A change of 10-20 points in WHO-5 has been proposed as a clinically relevant change (36, 49). In up-scaled interventions 60% lower effects are expected (50). We therefore aim at a difference of 12 points in the score between intervention groups and control group as well as between baseline and 6 months. A fluctuation in well-being is considered normal (36), subjects with well-being score  $>70$  are not expected to improve and will be excluded from the analysis. In the pilot study 21% of participants reached 70 points at baseline.

Desirable sample size was calculated to detect an effect of 12 points (36, 51) based on the assumption of two-tailed testing, an alpha error  $\alpha=0.05$  and power  $1-\beta=0.90$  and  $sd=19.9$  (48). To detect a medium standardised effect size of 0.5 (Cohen's d) for the primary outcome well-being at 6 months a sample size of at least 25 subjects per group is recommended. Expected drop-out rate due to withdrawal and lost to follow-up at six months is 75 %. Based on the expected drop-out rates and on excluding 20% from the analysis due to baseline score  $>70$ , we need to recruit at least 500 subjects to assure 25 subjects in each intervention arm. In the control group we assume subjects to be excluded based on using a digital product for behavior change and strive to include 200 subjects.

The secondary outcomes are exploratory due to the person-centred design of the service. The subjects will set individual goals and possibly change goals during the intervention. Likewise, habits and behavior change are largely changeable due to circumstances. The current research is not immense enough to guide a decision for minimal expected effects when individual goals are set (e.g., reducing weekly servings of red meat). A larger sample size than what is required for the primary

endpoint well-being is desired. Similarly, the secondary analyses of mediating factors and responsiveness require a large sample size. We therefore aim to include 5000 subjects.

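### The well-being analysis is labelled intention-to-treat, but its two-measurement rule and the omission of the month 1 and 3 WHO-5 scores leave the 6-month estimate resting on late responders

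*Protocol*

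**What the plan says.** Section 7.1 of the protocol states: "For the endpoint well-being an intention-to-treat approach will be applied". The next sentence sets the condition for entering the mixed model: "all subjects with two or more measurements will be included in the analysis and manual imputation is not needed". Section 7.3 specifies the model by intervention level and "time (0, 6, 12, 18 and 24 months").

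Table 1 (section 6.3.2) has a row for the "WHO-5 Well-being index" marked in all seven columns: months 0, 1, 3, 6, 12, 18 and 24. Section 4.5 adds that, as a safety measure, the index "will be sent out monthly to the user".

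The synopsis (section 1.6) places the primary endpoint at 6 months. On losses, section 7.4 says: "Expected drop-out rate due to withdrawal and lost to follow-up at six months is 75" per cent. On who is lost, section 6.3.1 accepts a risk of selection bias, because "highly motivated subjects (responders) possibly answer the questionnaires to a larger extent than subjects facing more challenges".

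Section 15 ends data collection at 7 months for controls and 25 months for subscribers. Section 6.2 says that people who stop using the app are asked to go on answering the questionnaires.

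**The concern.** An intention-to-treat analysis should keep every eligible subject. A mixed model that includes baseline as one of its time points can do this, because one score is enough to contribute. The two-measurement rule is therefore not required by the method, and it removes people because of what happened to them after enrolment.

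The list of model times adds to the problem. Doing without imputation is acceptable if loss is explained by the scores in the model. The scheduled scores best placed to explain loss before month 6 are those at months 1 and 3, and they are left out. A subject who answers at months 0, 1 and 3 and then stops has three scores on file, but at most the baseline score reaches the model. The protocol itself expects three quarters to be lost and expects responders to be selected. At stake is whether the 6-month result describes those who enrolled or those who kept answering.

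**Working it through.** **How many subjects carry the 6-month estimate.** Inputs from section 7.4: 20% excluded for a baseline score above 70, 75% lost at six months, 25 subjects needed per group.

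- The plan's own figure: 4 groups × 25 = 100, and 100 / (0.80 × 0.25) = 500 recruits. This reproduces the stated 500.
- Subscribers at the target: 5000 × 0.80 = 4000 eligible; 4000 × 0.25 = 1000 with a month-6 score; 3000 without.
- Controls, if the same rates apply (an assumption; no separate rates are given): 200 × 0.80 × 0.25 = 40.

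**What the rule does under the times in section 7.3.** A control can supply only months 0 and 6, so two measurements means both. The control estimate is then the mean change among completers. A subscriber needs two of months 0, 6, 12, 18 and 24, so must answer at month 6 or later. Section 7.1 does not say whether months 1 and 3 count towards the two. If they do, such a subject enters the analysis set but gives the model only a baseline score.

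**Illustration 1: change within one arm.** From section 7.4: SD 19.9, baseline mean 55, scores above 70 removed, 25% retained at month 6. Assumed: odds of staying multiplied by 1.35 to 2.72 per 19.9 points of improvement by month 3; correlation either 0.6 between all visits or 0.9 per month.

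| Analysis | Bias in mean 6-month change (points) |
|---|---|
| Responders at months 0 and 6 only | +1.4 to +5.6 |
| Months 0 and 6, baseline-only subjects kept | +1.1 to +4.7 |
| Months 0, 1, 3 and 6, all subjects | about 0 |

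The sign is not fixed. In the setting of illustration 2, when staying depended on the latest score rather than on change, the completers' one-arm change was 4.4 to 5.2 against a true 6.0.

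**Illustration 2: subscribers minus controls.** Assumed: true change 6 in subscribers and 0 in controls; SD 19.9; correlation 0.6; 70/45/25% of subscribers answering at months 1/3/6; odds of staying multiplied by 1.22, 1.49 or 1.82 per 10 points of latest score or of change.

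- Same loss in both groups: the contrast from months 0 and 6 was 5.9 to 6.1. There is no material bias.
- 70% of controls still answering at month 6 (assumed):

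| Analysis | Contrast (true 6.0) |
|---|---|
| Completers | 5.1 to 9.9 |
| Months 0 and 6, all subjects | 7.0 to 8.9 |
| Months 0, 1, 3 and 6, all subjects, both groups | 5.9 to 6.1 |

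The completers' contrast fell below 6 (5.1 to 5.5) when staying depended on score and rose above 6 when it depended on change. Keeping baseline-only subjects without adding months 1 and 3 did not remove the bias, so the two corrections belong together.

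**The case against.** Several objections stand and limit the point.

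- A reader might infer that everyone lost before month 6 is removed. The text does not say so. A subscriber who misses month 6 but answers at month 12, 18 or 24 stays in the model, and those who stop using the app are still invited to answer.
- A reader might infer that the plan overstates the benefit for subscribers. The protocol does not support that. The primary objective is a comparison with controls, and equal loss left that contrast unbiased. No separate loss is given for controls. Section 6.3.1 speaks of motivation, and only as a possibility; it does not mention improvement in well-being.
- The near-perfect recovery with months 1 and 3 is built into the simulations, because drop-out was generated from scores that the fuller model then uses. Real loss may also depend on scores never seen.
- The early scores are not thrown away altogether. Section 7.2 describes change at each follow-up. They are absent only from the model.
- Details of sensitivity analyses are commonly left to a statistical analysis plan, which is not at hand. The point does not rest on their absence.

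What the objections do not remove is that the label, the entry rule, the model times and the statement on imputation are all fixed in this protocol. A later analysis plan that followed them would inherit the problem.

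**Conclusion.** The point holds in a limited form. The label in section 7.1 does not match its own entry rule, and the times in section 7.3 leave out WHO-5 scores that Table 1 schedules. At the expected loss, the 6-month estimate rests almost entirely on people who answer at month 6 or later: about 1000 of 4000 eligible subscribers have a month-6 score. Under the section 7.3 times, the control estimate is a completers analysis.

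The change within one arm can be wrong by several points if staying depends on earlier scores, which matters against a 12-point target. The between-group contrast is at risk mainly if loss differs between subscribers and controls, and the error can go either way. All bias figures are illustrations. They rest on assumed correlations, retention patterns and drop-out mechanisms that the protocol does not give. The mismatch in the text does not depend on them.

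**What to change.** 1. Section 7.3: add months 1 and 3 to the WHO-5 model, with the same scheduled times in controls as in subscribers. Table 1 gives no separate schedule for controls, so confirm that it applies to them.
2. Section 7.1: delete the two-measurement rule and include every eligible consenting subject with any WHO-5 value. If the rule is kept, drop the intention-to-treat label.
3. Section 7.1: replace the remark on imputation with a statement that the model assumes data missing at random given the modelled scores, supported by a sensitivity analysis for missing month-6 scores.

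The cost is a few sentences and modest extra programming. For subscribers the scores are already scheduled. The early scores help the contrast only if both groups supply them. In the setting of illustration 2 with equal loss, using months 1 and 3 for subscribers alone turned a true contrast of 6.0 into 1.8 to 4.5. If controls will not be asked at those months, either extend their schedule or do not apply the early-score correction to one group only.

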### 7.2 Descriptive statistics

Figure 5 shows a logic model for the project with the anticipated predictors, mediators, intermediate outcomes, and endpoints. Descriptive statistics will be applied to report the reach of the intervention including demographics and user engagement patterns (analytics over time) for intervention dose. In addition, user engagement patterns will be specified for subgroups (age, gender, employment status, profession, educational level, residence in urban, rural, or semi-rural area and country of origin). The data will be examined for outliers, normality, and missing data. Mean and standard deviation will be given for normally distributed continuous variables, median and range for continuous variables with skewed distribution, and number and percentage for categorical and dichotomous values.

Change in mediators, intermediate outcomes and the endpoint well-being will be reported between baseline and each follow-up time point, presented by intervention group. Mean differences and standard deviations will be used for continuous variables and number and percentage change for categorical and dichotomous variables.

Figure 5. Logic model for the digital service LongLife Active showing the predicted underlying pathway and responses.

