#### 4.3 Risks associated with participation in the clinical investigation

Study subjects register for the digital service on the premises to use it as a consumer product, not to be involved in research. Upon registration a request to participate in the research study is shown in the app with information about the research study and obligations of participation (supplement 5a Forskningspersonsinformation). Study subjects consent to share their data for research purposes and will be asked to answer questions in the app that has been provided by researchers. This may cause stress and distraction to the user's intended use of the service for improved health and well-being, and increased concerns about private privacy as the data will be transferred to the researchers and used for research purposes.

Except for the before mentioned adverse device effect, no other risks have been identified for subjects in the clinical investigation.

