#### 5.2 Secondary objectives

II) To study internalization and implementation factors such as reach and dose of the medical device across 6 months.

III) To explore the impact of three different levels of digital support for healthy habits on reaching self-identified goals, dietary and physical activity habits, and mental health after 6 months.

IV) To explore determining response of sociodemographic factors in meeting the self-identified goal, dietary and physical activity habits, mental health, and well-being.

V) To evaluate the intended mediators (engagement with the service, improved motivation, self-efficacy, and reduced perceived barriers) of the medical device on achieving the self-identified goal, improved dietary and physical activity habits, mental health, and well-being.

VI) To explore what app functions and features mediate improvements of the medical device on behavior change, mental health, and well-being.

VII) To explore the engagement of using the digital service and adherence to behavior change across 24 months.

VIII) To explore the patterns of achieving the self-identified goal, change in motivation, dietary and physical activity habits, mental health, and well-being across 24 months.

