## 6.2 Subjects

### 6.2.1 Recruitment

The medical device will be launched and promoted by the company LongLife Active AB as a real-world project. The ambition is to reach individuals in need of lifestyle change, with a special emphasis on hard-to-reach groups. Health care services, pharmacies, employers, benefit platforms (e.g. Benify and Epassi) and social media will be targeted. Employers may apply for the health promoting subsidy, Friskvårdsbidrag, when employees sign up for LongLife Active. Health care patients prescribed physical activity (Fysisk aktivitet på recept, FaR) from their care provider is allowed a reduced fee on the membership of LongLife Active®.

Individuals who sign up for the service from September 2023, or as soon as ethical approval is obtained, will be informed about the research study and invited to consent for data extraction. Controls will be recruited through social media at the same time frame.

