#### *Inclusion criteria (intervention arms):*

- adults  $\geq 18$  years who sign up for the service LongLife Active using BankID for identification.
- consenting to the research study.

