#### *Reach*

Information on promotion channels and data on sales statistics will be collected from the provider. This data is not connected to the subjects. Demographics: age, gender, occupational status, profession, education, country of origin and living area, as well as a question on how the subject got information about the service will be collected by questions when signing up.

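### Reach and dose under Section 7.2 will describe users who consent to research and may not represent all users of the service; the data sources named in Section 6.3.2 cannot show whether they do

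*Protocol*

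**What the plan says.** Objective II in Section 5.2 of the protocol is "To study internalization and implementation factors such as reach and dose of the medical device across 6 months". Section 7.2 answers it descriptively: "Descriptive statistics will be applied to report the reach of the intervention including demographics and user engagement patterns". It also splits engagement by age, gender, employment, profession, education, type of residence area and country of origin.

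The data for this come from two sources, both set out in Section 6.3.2 under Reach:

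- **Provider data.** Promotion channels are recorded, and "data on sales statistics will be collected from the provider. This data is not connected to the subjects".
- **Subject data.** Demographics, and how the person heard of the service, are asked at sign-up. The text is worded for the study subject.

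Section 6.2.1 settles who is a subject. People who sign up "will be informed about the research study and invited to consent for data extraction", and the inclusion criteria for the intervention arms require "consenting to the research study". Section 4.3 explains why users and subjects are not the same people: "Study subjects register for the digital service on the premises to use it as a consumer product, not to be involved in research".

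Section 6.2.1 also gives the recruitment aim: "The ambition is to reach individuals in need of lifestyle change, with a special emphasis on hard-to-reach groups".

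**The concern.** Reach and dose of a device naturally refer to everyone who takes it up. Here a consent step stands between taking up the service and entering the data, and every individual demographic and engagement figure passes through it. Section 7.2 reports the result as the reach of the intervention. It names no denominator, no consent proportion, and no comparison of consenters with other users.

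Section 6.3.1 accepts a similar mechanism one step later, where it expects motivated subjects to answer questionnaires more often. It does not apply that reasoning to consent.

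The stake is a descriptive secondary objective, not the primary endpoint. Still, Section 3.1 says that reach and dose are seldom studied, and Section 6.4 foresees a published process evaluation of reach and engagement. Readers of that publication would want to know whether the service drew the people it was aimed at and how much they used it. The planned data answer this for consenters only.

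**Working it through.** **What the protocol fixes.** It states no consent rate, no number of all users, and no expected share of any group. There is no planned figure to reproduce, so the first step is to set the sections side by side.

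1. Objective II (5.2): reach and dose of the device. Natural population: all who sign up.
2. Recruitment and inclusion criteria (6.2.1): individual data come from those who consent.
3. Reach (6.3.2): data on all customers are promotion and sales figures without a link to subjects. Nothing shows that they carry demographics or use.
4. Descriptive statistics (7.2): demographics and engagement, with no denominator stated.

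From 2 and 3, the profile and engagement in 4 can be computed for consenters. No named source allows the same for all sign-ups. Section 7.2 does not itself say that it is restricted to consenters; this follows from the consent rule.

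**Possible effect on reach (illustration under assumptions).** Let s be a group's true share of all sign-ups and r its consent rate divided by that of other users. Its share among consenters is

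share = s·r / (s·r + 1 − s)

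For s = 0.20:

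- r = 0.5: 0.10 / 0.90 = 11.1%
- r = 0.75: 0.15 / 0.95 = 15.8%
- r = 1.0: 0.20 / 1.00 = 20.0%
- r = 1.25: 0.25 / 1.05 = 23.8%

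Over the same range of r, a true share of 10% appears as 5.3% (0.05 / 0.95) to 12.2% (0.125 / 1.025). A true share of 30% appears as 17.6% (0.15 / 0.85) to 34.9% (0.375 / 1.075). With equal consent (r = 1) there is no distortion. Above 1, the group is over-represented.

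**Possible effect on dose.** Let c be the overall consent proportion, m1 mean use in consenters and m0 mean use in the others. The mean over all users is c·m1 + (1 − c)·m0, so the consenters' mean differs from it by (1 − c)·(m1 − m0). With assumed consent of 30%, 50% or 80%, that is 0.7, 0.5 or 0.2 of the difference between the two groups. The protocol gives neither m1 nor m0.

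**How many users may be unobserved.** Section 6.2.1 expects 5000 consenters. At assumed consent of 30%, 50%, 80% or 100%, these come from 5000 / 0.3 = 16,667, 5000 / 0.5 = 10,000, 5000 / 0.8 = 6250, or 5000 sign-ups. The protocol does not say which is closer.

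**The case against.** Several objections are sound and limit the point.

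- **No misstatement is shown.** Bias needs consent to differ by group, and no rates are given. A reader might infer that the share of hard-to-reach users will be under-reported. The documents do not support this: the illustration gives no bias at equal consent and over-reporting when the group consents more often.
- **Objective II does not mention hard-to-reach groups.** They appear in Section 6.2.1 as an ambition for recruitment ("with a special emphasis on hard-to-reach groups"), without a definition or target share. No planned estimate for them is put at risk.
- **The provider's figures are not shut out.** They are collected under the Reach heading. Being unlinked, they could still give a denominator for overall uptake.
- **Demographics are asked at sign-up.** The text leaves open whether aggregates for all sign-ups could be obtained. Supplements that are not at hand may say more.
- **Consent limits any study that needs it.** No section claims that the results describe every user, so the general limit on applying the well-being result is not a finding here.

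It can also be said that a denominator and a consent proportion are matters for an analysis plan or a participant flow report. That stands for the definitions alone. It does not dispose of the point, because the gap lies in the data sources: if no aggregate of all sign-ups is arranged with the provider, a later analysis plan may have nothing to compare consenters with.

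**Conclusion.** The point holds as a limitation of what the planned data can show. Demographic reach and dose under Section 7.2 will describe consenting users, and the sources named in Section 6.3.2 cannot show whether these resemble all users. The size and direction of any difference are unknown. The figures of 11%, 16%, 20% and 24% for a true 20% rest entirely on assumed consent ratios and show only what could happen.

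The conclusion rests on one reading: that individual data on people who do not consent are unavailable to the researchers, as the consent rule implies. The matter is minor. It touches a descriptive secondary objective and leaves the primary comparison as it is. It is worth changing because the change is cheap and must be arranged while data are being collected.

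**What to change.** **Section 6.3.2, Reach.** Extend the provider's unlinked figures to an anonymous aggregate table of all sign-ups in the study period. Give counts by age band, gender and subscription level, and by any other sign-up items that are held and may be shared, such as education, country of origin and living area. Add weekly active users.

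**Section 7.2.** State the denominator for reach and for dose. Report the consent proportion overall and by the cells of the table, and compare consenters with all sign-ups.

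**Where aggregates cannot be obtained.** Limit the reach and dose conclusions explicitly to consenting users. This is a change of wording only.

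**Weighting.** Weighting consenters to all sign-ups is optional. Weights built on age, gender and subscription level would not correct for consent that differs by education, origin or living area if these are missing from the table, and should not be presented as doing so.

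**Cost.** One aggregate export per reporting period from a provider that already supplies unlinked figures, provided that it holds these items and may share them. Consent, questionnaires and sample size stay as they are. The drawback is that small cells must be merged to keep the table anonymous, which loses detail for the smallest groups.
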